**Fig. 1 Fig1:**
[figure not shown]
The flow diagram of the trial

**Fig. 2 Fig2:**
[figure not shown]
Standard Protocol Items: Recommended Items for Interventional Trials (SPIRIT). Template of content for the schedule of enrollment, interventions, and assessments in study 2.*

**Table 1 Tab1:** Measurement tools in studies 1 and 2

What	When	Study tool	Frequency
Study I	2017–18	Study 1 Form (EPJ)^a^	Once
		Study 2 Form (participant questionnaire)	Once
Study II	2015–19	“Calculating cost data”	Each consultation
		Interdisciplinary Wound Journal	Each consultation
		TIME^b^	Each consultation
		PWAT^c^	Each consultation
		SF-12v^d^	Baseline and 12 months/conclusion
		EQ-5D^e^	Baseline and 12 months/conclusion
		ISCI-QoL Data set^f^	Baseline and 12 months/conclusion
		SCIM III^g^	Baseline and 12 months/conclusion
	2018–2019	Observations, semi-structured interviews	Once

^a^*EPJ* electronic patient journal, ^b^*TIME* Time Infection Moisture Edge assessment scale, ^c^*PWAT* Photographic Wound Assessment Tool scale, ^d^*SF-12v* The 12-item Short Form Survey, ^e^*EQ-5D* Five Dimensions European Quality of Life scale, ^f^ISCI-QoL Data set The International Spinal Cord Injury Quality of Life Data set, ^g^*SCIM III* The Spinal Cord Injury Measurement scale, version III

The RCT part of the protocol conforms to the Consolidated Standards of Reporting Trials (CONSORT) guidelines extensions for randomized pilot and feasibility trials [15]. The study design is shown in the flow diagram in Fig. 1. The timeline for study enrollment, intervention, and assessment is described in the Standard Protocol Items: Recommendations for Interventional Trials (SPIRIT) [16] in Fig. 2. A SPIRIT Checklist [16] is included as Additional file 1. A summary of the questionnaires and forms is shown in Table 1.

### Ethical approval

The research project will be carried out in accordance with current ethical guidelines for health services in Norway [17], based on the Code of Ethics of the World Medical Association (Declaration of Helsinki) [18] for experiments involving humans. The research project was approved by the Norwegian Regional Ethical Committee (REC) on 9 January 2015 (2014/684 REK Nord), and registered at ClinicalTrials.gov in May 2016 (NCT02800915). The privacy rights will be followed throughout the study. Communication takes place through the Norwegian Health Network (Norsk Helsenett) using encrypted software (Cisco Meeting). The investigators will obtain informed consent from all participants before inclusion. The videoconferencing connection will be initiated from the departments offering specialized SCI rehabilitation and must be approved by the patient before log on. All videoconferencing takes place in real time and neither sound nor images are recorded or archived. The teleSCI project meets the standards and rules set by the Norwegian Data Protection Authority [19]. PUs often occurs near intimate body areas, and these areas may be visible on the screen for the participants in the intervention group. This was an ethical issue that was especially emphasized in the feasibility study [11]. The knowledge and expertise from the pilot project will be continued in the current study. Researchers from the “Distributed Home Care Solutions project” [20] also participated in the feasibility project. This ensured continuous assessment of ethical issues and user interaction throughout the project. Experience and knowledge from this cooperation has been implemented in the current research project. The Norwegian standard for information security in the health sector will be followed [19].

### Participants

#### Study 1

The epidemiological study includes all persons hospitalized at the three specialized SCI departments in Norway for primary rehabilitation from 1 January 2004 to 1 January 2014. All relevant persons identified will receive a questionnaire focusing on past and present PUs (Table 1). The study will run from January 2017 to May 2018 (Fig. 1).

#### Study 2

Sixty persons with SCIs and ongoing PUs, as well as their relatives and local caregivers, will be included in a RCT (Fig. 1). The participants will be randomized into two groups with 30 persons in each group. One group, their relatives and local caregivers will be offered regular, interdisciplinary, outpatient follow-up by the SCI department’s wound team at Haukeland University Hospital and at Sunnaas Rehabilitation Hospital via videoconferencing, telephone, and consultations at the outpatient wound clinic at the hospital (the teleSCI group). The other group, their relatives and local caregivers will receive guidance by the SCI department’s wound team at Haukeland University Hospital or Sunnaas Rehabilitation Hospital, based on existing routine. The follow-up will be offered by telephone and visits at the outpatient wound clinic at the hospital, based on request from the local caregivers or the patient. (the usual care group). The RCT will run from June 2015 to July 2019 (Fig. 1).

### Procedures

#### Identification

The participants in study 1 will be identified during an epidemiological multicentre study where the aim is to find the cumulative incidence of SCIs in Norway for the years 2004–2014, as well as to register the prevalence of PUs in this group. The time period for study 1 is January 2017 to May 2018, and the settings are all three specialized SCI departments in Norway. These three SCI departments have a life-long follow-up responsibility for all persons with SCIs living in Norway; the participants will, therefore, be recruited from municipalities from all over the country. Individuals with a SCI and present PUs found in study 1 will be invited to participate in study 2. In addition, the participants in study 2 will also be identified from patients with SCIs, currently hospitalized or referred to the outpatient clinics at the specialized SCI departments because of PUs (Fig. 1). All potential participants will be invited to be enrolled in study 2. The follow-up period will be until ulcer healing or after maximum 12 months from baseline. The settings of the RCT will be the specialized SCI department at Haukeland University Hospital and Sunnaas Rehabilitation Hospital, as well as municipalities from all over Norway (Table 2).

**Table 2 Tab2:** The intervention illustrated by main features from the Template for Intervention Description and Replication (TIDieR) Checklist and Guide

*Brief name*: outpatient treatment of pressure ulcer from home by teleSCI	
*Why*: to improve the outpatient follow-up in persons with spinal cord injury (SCI) and pressure ulcer	
*What*: outpatient pressure ulcer follow-up from the participant’s home, using videoconferencing as a tool to cooperate, compared to usual care. The therapy will be tailored from the specialized health care system to the participant’s home in cooperation with the local caregivers, with focus on wound healing, quality of life, cooperation, user participation, and costs	
*Who provided*: the SCI wound team, consisting of a physician, a wound nurse, and an occupational therapist sited at Haukeland University Hospital and Sunnaas Rehabilitation Hospital. A plastic surgeon and an Ortopedic physician will be included in the wound team when necessary. The local caregivers will receive training via videoconferencing in how to treat and prevent pressure ulcer among the group of persons with spinal cord injury within the context of a clinical trial	
*How*: using videoconferencing and remote control software to a laptop at the patient’s location	
*Where*: from Haukeland University Hospital and Sunnaas Rehabilitation Hospital to the patient’s home	
*When/how much*: the experimental intervention consists of pressure ulcer treatment guidance every second or third week until the pressure ulcer has healed, or a maximum of 52 weeks.	

### Drop outs

Participation is voluntary, and withdrawal is possible at any time. The participants will still be allowed to complete follow-up treatment for their PU through the specialized health care service. Participants who for various reasons need to be hospitalized during follow-up, e.g., if needed treatment cannot be provided by local care services, or if surgery is needed, will be excluded from the study during their period of hospitalization. Length of admission and cause will be registered and the participants will be included in the study again after being dismissed from the hospital.

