##### Primary endpoints

Study 2 will focus on the effect of using teleSCI compared with other outpatient approaches in the follow-up of persons with PUs after a SCI, measured in terms of percentage wound size healed, and the time to heal. A systematic evaluation of the ulcer will be done, using the validated Time Infection Moisture Edge (TIME) form [26] and the Photographic Wound Assessment Tool (PWAT) scale [27], where the amount of fibrin and granulation tissue present, percentage of epithelialization of the wound, percentage of moisture present, and the appearance of the wound edges will be described. Time to heal will be measured counting days until healing, or measuring the amount of healing at the end of the 12-month follow-up period. Changes in self-reported health-related quality of life (HRQoL) and the need for assistance will be compared using the 12-item Short Form Health Survey (SF-12v) [28], the Five Dimensions European Quality of Life scale (EQ-5D) [23], and the International Spinal Cord Injury Quality of Life questionnaire (ISCI-QoL) basic data set [29]. The SF-12v [28] measures functional health and well-being from the patient’s point of view. The EQ-5D scale [23] measures mobility, self-care, activities, pain, discomfort, and anxiety/depression. The participants perform a self-rating of their health in a box-scale and on a vertical visual analog scale. In the ISCI-QoL questionnaire [29], the participants will rate their physical and psychological health, using a box-scale. The SF-12v [28], EQ-5D [23], and ISCI-QoL [29] will be used as a quantitative measure of the health outcome that reflects the participant’s own health judgment before and, at the end of, the follow-up period. The Spinal Cord Independence Measure, version III (SCIM III) scale [24] has been designed specifically for persons with SCI and is a comprehensive ability-grading scale, focusing on the ability of performing basic tasks, and the effect the SCI has on the overall medical condition and comfort. SCIM III [24] will be rated at baseline and at the end of the follow-up period, and the results from both groups in the RCT will be compared with focus on changes in performing ability during the follow-up period.

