### Adverse events

Adverse events or other unintended effects of trial interventions or trial conduct in the RCT will be collected, assessed, and reported in accordance with Norwegian legislation [30]. These possible events and effects will be reported in the trial outcomes. If the PU does not heal during the follow-up period, the participant will be invited to further follow-up also after the termination of the RCT.

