### Intervention

In our previous feasibility study [11] one of the important factors regarding PU healing was that the follow-up was performed by a few dedicated homecare nurses, as this continuity resulted in a better overall overview of the follow-up. The feasibility study also showed the importance in using a simple, common description of the PU status and the plan for the further treatment. These principles will be continued for both groups in the RCT.

The location and grade of the PU, and comorbidities influencing the healing process, will lead to individualized follow-up for each participant. In case of adverse effects, or worsening of the PU, necessary therapeutic measures will be initiated to prevent further worsening of the condition. If needed, surgical treatment or inpatient care will be recommended. All adverse events and worsening of the condition will be recorded in the wound journal and in the report form. In case of bacterial infection of the PU, laboratory tests will be performed, and the participant and the general practitioner will be informed. The local caregivers will be informed with permission from the participant.

An interdisciplinary wound journal has been drafted to map current age, marital status, socioeconomic status, lifestyle factors, nutritional information, and additional conditions that may affect ulcer healing. The wound journal also contains a follow-up part where the PU and recommended treatment measures, including cushions, mattresses, pressure relief, and positioning, are continuously registered at every wound session. The wound journal was used during the feasibility study, and necessary changes were done, based on feed-back from the interdisciplinary wound team at the hospitals, and the participating patients. The questionnaire forms and time lapse of the RCT are shown in Table 1.

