### Statistical analysis

Data from the end of the study will be analyzed using chi-square tests for categorical data and *t* tests for continuous data. Regression analyses (linear and logistic) will be performed to make any necessary adjustments for baseline differences. In addition, we will also analyze developments over time in the two groups, using the mixed-models analysis.

Mean QoL scores with corresponding 95% confidence interval will be estimated in each of the two treatment groups, and the groups will then be compared using *t* tests and mixed-models analysis. A cost-benefit analysis will be carried out to assess the cost of outpatient treatment via telemedicine, compared with outpatient treatment at the hospital.

The reduction (in percentage) of PU size is calculated with corresponding 95% confidence interval for each of the two treatment groups. The groups will be compared with regard to percentage reduction in ulcer size, using *t* tests and mixed models. All quantitative statistical analyses will be performed using the SPSS and STATA statistical software package. Computer Assisted Qualitative Data Analysis (CAQDAs) will be used in the qualitative analysis.

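### Suspending participants from the study during hospital admission is outcome-related and conflicts with a calendar count of time to heal; separately, the cost comparison leaves inpatient stays out

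*Protocol article*

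**What the plan says.** Drop outs gives as examples of reasons for admission "if needed treatment cannot be provided by local care services, or if surgery is needed". Participants so admitted "will be excluded from the study during their period of hospitalization". It continues: "Length of admission and cause will be registered and the participants will be included in the study again after being dismissed from the hospital".

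Intervention links such admissions to the course of the ulcer. After describing measures for adverse effects or worsening, it adds: "If needed, surgical treatment or inpatient care will be recommended". It also says: "All adverse events and worsening of the condition will be recorded in the wound journal and in the report form".

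Primary endpoints defines the effect as "measured in terms of percentage wound size healed, and the time to heal". Time to heal is a count of days to healing, or the amount healed at 12 months. Under Identification, the limit on follow-up is set at 12 months from baseline.

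On cost, Statistical analysis says: "A cost-benefit analysis will be carried out to assess the cost of outpatient treatment via telemedicine, compared with outpatient treatment at the hospital". The contacts to be counted under Secondary endpoints are teleSCI consultations, hospital outpatient appointments and telephone calls. Travel, working time lost, medication, bandages and emissions are also recorded. Neither an inpatient stay nor surgery is listed.

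**The concern.** The suspension is triggered by something that happens after randomisation and that can be a consequence of the outcome under study. It may also depend on the arm. The teleSCI group is seen by the wound team at intervals of two to three weeks, whereas contact in the usual care group depends on the local service, the patient or next of kin. A team that sees the wound regularly may refer to hospital earlier, more often or less often than one contacted on request. Equal admission in the two arms cannot be assumed.

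If the suspension is applied literally to the primary endpoint, the accounting is lopsided. Days in hospital leave the count, while any reduction or closure achieved there is still present when the wound is next measured and is attributed to outpatient follow-up. An arm with more admissions could then appear to heal faster.

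The cost comparison has a related gap with a different source, namely its outpatient-only scope. Hypotheses expects teleSCI to save money and time against traditional hospital treatment, and the Discussion expects lower use of hospital services. A comparison without admissions cannot properly test either expectation, and it could favour an arm that generates more of them.

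**Working it through.** **1. The plan's own figure.** Sample size gives 25 per group for a standardised difference of 0.8 at 80% power. No alpha is stated; I assume two-sided 0.05. Then n = 2 × (1.960 + 0.842)² / 0.8² = 2 × 7.85 / 0.64 = 24.5, so 25 per group. Enrolling 30 tolerates a loss of 5/30 = 16.7%. The figure reproduces. It is used here only as a yardstick of 0.8 SD.

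**2. The sections side by side.**

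| Question | Drop outs | Primary endpoints / Identification |
|---|---|---|
| Do hospital days count in time to heal? | Out of the study while admitted | Days to healing, nothing subtracted |
| When does follow-up end? | Suspended and resumed | 12 months from baseline |
| How is an ulcer closed in hospital classified? | Not stated | Not stated |

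The first two rows cannot both be applied literally to an admitted participant.

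**3. One participant (illustration).** Suppose an ulcer worsens at day 90 and is closed during a 60-day stay. Counted in calendar days, it heals at 90 + 60 = day 150. Counted in days on study, it heals at about day 90. For an ulcer that does not heal, a suspended clock would move the 12-month limit from day 365 to day 365 + 60 = 425. A 60-day stay is 60/365 = 16% of the horizon.

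**4. Comparison of arms, if hospital days are dropped.** Shift in mean time to heal = (difference in admission share) × (mean stay), taking the same mean stay in both arms. The documents give neither quantity, so both are assumed.

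| Admission shares | Stay 14 d | Stay 30 d | Stay 60 d |
|---|---|---|---|
| 10% vs 10% | 0 | 0 | 0 |
| 20% vs 10% | 1.4 | 3.0 | 6.0 |
| 30% vs 10% | 2.8 | 6.0 | 12.0 |
| 40% vs 10% | 4.2 | 9.0 | 18.0 |

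The last row, divided by an assumed SD of 100 or 60 days, runs from 4.2/100 = 0.04 to 18/60 = 0.30 SD, against the design effect of 0.8 SD.

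**5. Cost.** The omitted cost difference per participant is (difference in admission share) × (mean stay) × (unit cost per inpatient day), plus any surgery. The table therefore also gives the omitted inpatient days: 0 to 18 per participant. The documents give no unit cost, so no monetary figure can be stated.

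**The case against.** The best defence is that the sentence under Drop outs means only that trial sessions and assessments pause while calendar time runs on. Primary endpoints subtracts nothing, and Identification anchors the limit at baseline. That reading is available and would remove the problem for time to heal. But the article's words take the participant, not the sessions, out of the study, and they appear as a stated rule rather than as a detail left to an analysis plan. The conflict stands; that the clock stops is only one reading of it.

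A reader might infer that the worst outcomes are removed from the trial. The documents do not support this. The exclusion is temporary, wound size, quality of life and function at the end of follow-up remain analysable, and worsening and the cause of admission are recorded. On adverse events, the article says "These possible events and effects will be reported in the trial outcomes". Nor does it say that readmitted participants lack an endpoint value. If they did, power by normal approximation would fall from 87% with 30 per group to 79% with 24, but that is not what is written.

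Three further points stand. Admissions may occur for various reasons, so not every one reflects a failing ulcer. The cost gap comes from the outpatient-only scope under Secondary endpoints and Statistical analysis, so rewording Drop outs alone would not close it. And the hospital treatment named in Hypotheses may mean hospital outpatient care; even so, admissions arising under either form of follow-up belong to the cost of that follow-up.

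How to classify surgical closure in the main analysis is a choice between defensible options and does not carry this point.

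**Conclusion.** The concern holds in a limited form. The article fixes an outcome-related suspension after randomisation, and its literal effect on time to heal conflicts with counting from baseline. Separately, the cost comparison leaves out inpatient stays, although their length is registered.

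Neither the direction nor the size of the bias is known. Within the assumed ranges the shift in mean time to heal is 0 days with equal admission rates and equal stays, and at most 18 days per participant (40% against 10%, 60-day stays). That maximum is 0.18 to 0.30 SD for an assumed SD of 100 to 60 days. These figures apply only if hospital days are dropped from the count. It would go too far to call the randomised comparison broken, or to say that one arm is favoured. The cost gap does not depend on how Drop outs is read.

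**What to change.** - Replace the exclusion wording under Drop outs. Only trial sessions pause during admission; all randomised participants stay in the analysis of their assigned group; time to heal and the 12-month limit run in calendar days from baseline through any admission. Align Identification and Primary endpoints with this.
- Report admissions, inpatient days and surgery by arm. State in advance how an ulcer closed in hospital is classified, with a sensitivity analysis using the alternative classification.
- Add inpatient cost to the cost comparison, as registered length of stay times a unit cost, and amend its outpatient-only scope accordingly.

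These are changes to accounting and analysis; none alters clinical care. The cost is small but more than wording. Length and cause of admission are registered, but the article does not say that admission or closure dates are, so a record look-up is needed for participants already followed, and unit costs must be obtained. Trial status reports about 50 participants randomised, nearly 40% of them finished (about 0.4 × 50 = 20), and data entry not yet begun, so the rule could be settled before analysis.

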### Feasibility

The investigators conducted a feasibility study to explore the PU management by teleSCI before the current research project [11]. Wound healing, satisfaction, cost-benefit, and feasibility were mapped through logs, questionnaires, and semi-structured interviews with seven participants and their local caregivers. The results were promising, indicating that teleSCI is an acceptable and safe way to offer follow-up with regards to the technical solutions. Validated forms mapping QoL and function were used [21–23], as well as custom-made forms to map costs and participant satisfaction. Based on feed-back from the participants in the feasibility study [11], the forms have been improved to suit the current project.

### Screening for eligibility, baseline assessment, and recruitment

The epidemiological information concerning all relevant participants will be collected from the electronic patient journal (EPJ) system at the three SCI departments by the main investigator. The *World Health Organization (WHO) International Classification of Diseases (ICD)* [24] will be used to identify SCI-related conditions (Additional file 2). All current persons identified will receive a questionnaire focusing on past and present PUs.

### Study 1

